**Biomarker**											
Biospecimen	whole blood, urine, stool, saliva	**×**	**×**	**×**			**×**		**×**		**×**
Neuroimaging	Resting-state fMRI, T1, DTI, Tasks	**×**		**×**			**×**		**×**		**×**
EEG	Resting state EEG, Tasks	**×**		**×**			**×**		**×**		**×**
Digital phenotyping	Portable EEG, heart rate, body temperature, sleep, voice, facial expression, eye movement, gait	**×**		**×**			**×**		**×**		**×**

^a^Additional visits for precision medicine cohort. *W* week

#### Sociodemographic information and lifestyle habits

Sociodemographic information will be collected through a structured self-report questionnaire at baseline, including birth date, gender, height, weight, marital status, education level, occupational status, household income, living area, left-behind children experience and experience of being an only child. Also, data on lifestyle and dietary habits such as defecation, smoking, drinking, dietary habits, water intake and the use of antibiotics and probiotics will be collected. Information will also be collected about the history of the present illness, physical examination results, comorbidities, treatments and adverse events.

#### Clinical assessment

Participants will be interviewed and diagnosed by a psychiatrist at baseline using the Mini-International Neuropsychiatric Interview (MINI). Diagnosis will be classified according to DSM-5 and MINI as depression with anxious distress, mixed features, melancholic features, atypical features, psychotic features, seasonal pattern or peripartum onset.

The following scales will be used to assess clinical symptoms and function at baseline: the HAMD-17 (Hamilton, 1960; Zheng *et al.*, 1988), Hamilton Anxiety Scale (HAMA) (Hamilton, 1959; Tang and Zhang, 1984), Brief Psychiatric Rating Scale (BPRS) (Faustman and Overall, 1999), Columbia-Suicide Severity Rating Scale (C-SSRS) (Posner *et al*., 2008), Bipolarity Index (BPX) (Ma *et al.*, 2016) and Modified Apathy Estimate Scale (MAES) (Starkstein *et al.,*
1992).

The self-report measures include the Quick Inventory of Depressive Symptomatology-Self-Report (QIDS-SR16) (Liu *et al*., 2013; Rush *et al*., 2003), Snaith-Hamilton Pleasure Scale (SHAPS) (Snaith *et al*., 1995), Generalized Anxiety Disorder-7(GAD-7) (Hidalgo and Sheehan, 2012), Perceived Deficit Questionnaire for Depression 5-item (PDQ-5) (Shi *et al.*, 2017; Sullivan *et al.*, 1990), Hypomania Check List (HCL-33) (Feng *et al.*, 2016; Wang *et al*., 2018), Frequency and Intensity of Side Effects Rating/Global Rating of Side Effects Burden (FISER/GRSEB) (Wisniewski *et al.,*
2006), Patient-Rated Inventory of Side Effects (PRISE) (Rush *et al.,*
2004), Patient Adherence Questionnaire (PAQ) (Mojtabai *et al*., 2012), Sheehan Disability Scale (SDS) (Sheehan, 1986), Childhood Trauma Questionnaire (CTQ) (Bernstein *et al.*, 2003), Eysenck Personality Questionnaire (EPQ) (Eysenck and Eysenck, 1975; Gong, 1984), Remote Follow-Up Checklist (RFC), Patient Health Questionnaire (PHQ-9) (Kroenke *et al.*, 2001; Wang *et al.,*
2014), Mood Disorder Questionnaire (MDQ) (Hirschfeld *et al.*, 2000), Ask Suicide-Screening Questions (ASQ) (Horowitz *et al.,*
2012), Life-chart Methodology (LCM) (Denicoff *et al.*, 2000), Migmine Disability Assessment Questionnaire (MIDAS) (Stewart *et al*., 2001), Headache Impact Test-6 (HIT-6) (Kosinski *et al.,*
2003), Chalder Fatigue Scale-11 (CFS-11) (Chalder *et al.,*
1993) and Perceived Stress Scale (PSS) (Cohen *et al.*, 1983).

#### Biospecimen collection

Biospecimens, including blood, urine, feces and saliva, will be collected to explore multi-omics interactions and reveal the pathophysiology of depression. Blood samples will be collected at baseline and scheduled visits with one pro-coagulation blood tube (6 mL), one PAXgene® Blood RNA Tube (2 mL) and two EDTA anticoagulation blood tubes (6 mL/tube). Urine samples will be collected with a urine cup (40 mL). A standardized kit (25mL) will be provided to collect fecal samples and maintain their integrity. Saliva samples will be collected with sterile, nuclease-free 5-mL conical screw-cap tubes. All blood, urine and fecal samples will be stored in −80°C freezers and transported through the cold chain to the PROUD biobank.

#### Cognitive assessment

The Chinese Brief Cognitive Test (C-BCT) will be used to assess four cognitive domains: speed of processing, attention, reasoning/problem-solving and working memory. The psychometric properties of the C-BCT are well-established, including large norms, test-retest reliability and consistency across cultures. Moreover, it has been validated against traditional paper-and-pencil tests that assess equivalent domains (Ye *et al.,* 2022).

#### Neuroimaging data

Neuroimaging will include T1- and T2-weighted structural imaging, fluid-attenuated inversion recovery (FLAIR), diffusion-weighted imaging (DWI), susceptibility-weighted imaging (SWI), resting-state functional MRI (fMRI) and diffusion tensor imaging (DTI). Anatomical and microstructural imaging will include a 3D high-resolution magnetization-prepared rapid gradient-echo (MPRAGE) sequence and a 64-direction diffusion tensor imaging sequence, respectively. Both resting-state and task-based fMRI data will be collected as part of the functional imaging protocol. The task-based BOLD fMRI signal will be used to analyze reward processing and emotional regulation.

Quantitative imaging, melanin imaging, arterial spin labelling and task-based fMRI will be optional in the PMC study. The task-based fMRI will include rumination, emotional recognition and social cognition tasks. All MRI scans will be performed using a 3.0T scanner (Siemens, GE and Philips) by trained investigators following a standardized protocol.

#### Electroencephalogram data

EEG data will be acquired using standard pre-specified hardware and software. The resting EEG will be recorded in two 5-min sessions while participants are relaxed with eyes open or closed. Event-related potentials (ERPs) will be elicited by activation tasks. The face-word Stroop paradigm was employed to assess cognitive and emotional regulation. The experiment requires a quiet environment with a comfortable temperature and humidity level and electromagnetic shielding. The EEG data will be recorded using the Neuroscan and Brain Products with 64 electrodes.

#### Digital phenotype data

Digital phenotype data, including portable EEG, heart rate, body temperature, sleep and other parameters, will be collected using wearable devices during daily life. Eye movement, gait, voice and facial expressions will be collected in the hospital during the visits, as the collection of these data requires space and specialized equipment.

### Follow-up strategies

#### General follow-up strategies for PROUD

All participants of the PROUD cohort study will be followed up by trained investigators at least once a year for at least 3 years, through a combination of field visits, remote visits, telephone visits and patient self-reporting.Field visits: All patients will be required to make field visits at baseline and at the end of years 1, 2 and 3 (Table 1). Demographic, clinical, biological, neuroimaging, EEG and digital phenotype data will be collected. If a patient is unable to make a field visit at the scheduled time due to extenuating circumstances, a telephone visit will be performed by an investigator.Remote visits: A remote follow-up visit will be conducted by sending a RFC to the patient via a mobile device every 4 weeks to capture patient mood swings. The checklist includes seven questions on depression, anxiety, suicide/self-injury and mania/hypomania.Telephone visits: Telephone visits will be conducted every 3 months to gather information on mood conditions, treatments, medication use and outcomes to ensure patient compliance and to acquire timely information regarding their condition.Patient self-reports: Patients will actively report their conditions, such as mood swings, somatic diseases, treatment information and adverse events, via WeChat, SMS, telephone calls and in-person visits to the hospital.

#### Additional follow-up strategies for PROUD-PMC

PROUD-PMC is based on PROUD's follow-up strategies but with extra field visits at the end of weeks 2, 8 and 12. The frequency of remote visits is increased to once every 2 weeks throughout the first year. PROUD-PMC includes external visits to capture the critical points in depression progression and chart the disease trajectory. After 12 weeks, all PROUD-PMC cohort study participants will be followed up by sending regular RFC reminders via a mobile device (see the section on remote visits). An external visit will be scheduled if the RFC scores reach certain thresholds. The logic diagram of external visits can be found in Figure 2.If the combined score of RFC items 1 and 2 or of items 3 and 4 is ≥ 3, the PHQ-9 will immediately be delivered to the mobile device. An external visit will be scheduled if the difference between the total PHQ-9 score at that time and the previous total score is ≥ 5, indicating possible depression relapse or recurrence. A decrease in the PHQ-9 score of ≥ 5 points may indicate amelioration of the patient’s depressive condition.If RFC item 5 is scored ≥ 2, the ASQ will be delivered immediately and an answer of “yes” for any of items 3–5 indicates high risk of suicide and an external visit will be requested.If the answer to RFC item 6 or 7 is "yes", the MDQ will be delivered immediately. If ≥ 7of the MDQ's 13 screening symptoms are present, indicating risk of mania/hypomania, an external visit will be scheduled.

**Fig. 2 Fig2:**
[figure not shown]
Logic diagram of external visits

The external visit will be in the form of a field visit which consists of the following: (1) Re-evaluation of the relevant module of the MINI; (2) Collection of information on psychiatric history, physical examination results, somatic diseases, treatment and adverse events; (3) Scale assessment; (4) Re-evaluation of the event that prompted the external visit; (5) Cognitive assessment and (6) Collection of biospecimen and multimodal data, including EEG, neuroimaging and digital phenotype data. These data will only be collected once if a patient has two or more risk events of the same type throughout the follow-up period.

### Outcomes

#### Primary outcomes

Primary outcomes are depressive symptom changes, as measured by the HAMD-17 total scores in the acute, maintenance and long-term follow-up phases compared with baseline. Clinical efficacy in different phases is defined as follows:Early onset rate: a reduction of HAMD-17 total score ≥20% from baseline by the end of week 2.Response rate: a reduction of HAMD-17 score ≥50% from baseline. Additionally, a stable response is defined as a reduction of two consecutive HAMD-17 total scores ≥50% from baseline at weeks 8 and 12.Remission rate: a HAMD-17 score ≤7 in the acute phase. Stable remission is defined as two consecutive HAMD-17 scores ≤7 at weeks 8 and 12.Relapse: a HAMD-17 score ≤7 or a reduction of HAMD-17 score ≥50% at the end of the acute treatment, lasting for <2 months, followed by a HAMD-17 score ≥14 in combination with meeting the diagnostic criteria for MDD of DSM-5.Recurrence: a HAMD-17 score ≤7 at the end of the acute treatment, lasting for >2 months, followed by a HAMD-17 score ≥14 in combination with meeting the diagnostic criteria for MDD of DSM-5.

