### Additional inclusion criteria for PROUD-PMC

Males and females aged 18-65 years.A score of ≥14 on the 17-item Hamilton Depression Rating Scale (HAMD-17) at both screening and baseline.Have not taken any antidepressant agents for at least 14 d before screening (fluoxetine therapy should be discontinued at least 28 d before screening).Monotherapy for antidepressants planned.

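### A responder who never remitted, whose response lasts more than 2 months and who then returns to full MDD, is neither a relapse nor a recurrence

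*Protocol article*

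**What the plan says.** The Primary outcomes section of the protocol article first names the change in HAMD-17 from baseline and then lists derived efficacy outcomes. Four of these matter here.

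- Response: "Response rate: a reduction of HAMD-17 score ≥50% from baseline". No absolute score is required.
- Remission: "Remission rate: a HAMD-17 score ≤7 in the acute phase".
- Relapse: "Relapse: a HAMD-17 score ≤7 or a reduction of HAMD-17 score ≥50% at the end of the acute treatment, lasting for <2 months", and then a worsening.
- Recurrence: "Recurrence: a HAMD-17 score ≤7 at the end of the acute treatment, lasting for >2 months, followed by a HAMD-17 score ≥14".

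Relapse and recurrence share the same worsening criterion: "followed by a HAMD-17 score ≥14 in combination with meeting the diagnostic criteria for MDD of DSM-5".

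Entry to the PMC requires "A score of ≥14 on the 17-item Hamilton Depression Rating Scale (HAMD-17) at both screening and baseline". Its follow-up section adds "extra field visits at the end of weeks 2, 8 and 12", and Table 1 also marks weeks 24, 76 and 128 as PMC visits. For the whole cohort, "All patients will be required to make field visits at baseline and at the end of years 1, 2 and 3". The Data analysis section says that prediction models will be built for the primary and secondary outcomes.

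**The concern.** The two definitions read as a pair split at 2 months, but the set of patients they admit changes at the split. Below 2 months, remission or response qualifies. Above it, only remission does. A patient who responded without remitting and kept that response beyond 2 months can later have a confirmed return of MDD for which the outcome list has no name.

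The study sets out to chart the course of MDD and to model these outcomes. An event outcome that leaves out confirmed returns among incompletely recovered patients does not describe that course. If such patients also entered an analysis as event-free, relapse and recurrence rates would come out too low in this group, and a model fitted to them would understate the risk that goes with residual symptoms.

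**Working it through.** The plan states no figure to reproduce. The check is logical, with a little arithmetic on scores and visit times.

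**Step 1: cross the state with its duration.** Inputs: the relapse and recurrence definitions in the Primary outcomes section. Assume in every cell that the patient later reaches HAMD-17 ≥14 with DSM-5 MDD.

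| State at end of acute treatment | Lasted <2 months | Exactly 2 months | Lasted >2 months |
|---|---|---|---|
| HAMD-17 ≤7 | relapse | neither | recurrence |
| ≥50% reduction, score above 7 | relapse | neither | **neither** |

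Because the state is fixed at the end of acute treatment, a literal reading also leaves out a lasting responder who first falls to 7 or below after that point.

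**Step 2: can the empty cell hold patients?** A responder who is not in remission needs a score *e* with *e* ≥ 8 and *e* ≤ *b*/2, where *b* is the baseline score. This is possible only if *b* ≥ 16.

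- *b* = 14: *e* ≤ 7, so every responder is in remission.
- *b* = 15: *e* ≤ 7.5, so again every responder is in remission.
- *b* = 16: *e* = 8.
- *b* = 20: *e* = 8 to 10.
- *b* = 24: *e* = 8 to 12.

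The PMC admits from 14 upwards, so the cell is empty at baselines 14 and 15 and open at every higher baseline.

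**Step 3: does the schedule reach the cell?** The article does not fix the week in which acute treatment ends, so take week 8 and week 12 as alternatives, with 30.44 days per month.

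- End at week 12: weeks 12 to 24 are 12 × 7 / 30.44 = 2.8 months.
- End at week 8: weeks 8 to 24 are 16 × 7 / 30.44 = 3.7 months.

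Under either assumption, a response held continuously to the week 24 visit has lasted more than 2 months. If such a patient is still above 7, any later return found at weeks 52 to 156, or at an external visit, has no category.

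**Step 4: does another section close the gap?** No. The PMC follow-up section mentions relapse or recurrence only as what a rise in PHQ-9 may indicate when it prompts an external visit. It defines no event.

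**Step 5: how many patients?** This cannot be computed. The article gives no response rate, remission rate or HAMD-17 distribution for this cohort.

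**The case against.** Four points can be made on the other side.

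**The 2 months describe the state, not the date of the event.** A reader might infer that any non-remitting responder who worsens after 2 months goes uncounted, so that such patients can have an event in only 8.7 of the 144 weeks from week 12 to week 156. The text does not support that. The duration attaches to the response or remission, and the later score of 14 or more has no deadline. Take baseline 20 and a score of 10 at the end of acute treatment. If the score drifts within 2 months to 11 (reduction 9/20 = 45%) or 13 (7/20 = 35%), the response has ended. If it reaches 14 with MDD at month 6, the relapse definition is still met. This objection stands, and it limits the gap to responses that themselves last more than 2 months.

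**The worsening is not lost.** The HAMD-17 change from baseline includes it, hospitalization may record it, and PMC external visits are triggered whatever the earlier state. This also stands. The gap concerns the two named events only.

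**The restriction may be deliberate.** The response alternative is written into one definition and left out of the other, so recurrence may be meant for remitters alone, with other responders outside its risk set. That is possible, but the article does not say so, and relapse still gives these patients no category once the response has lasted 2 months.

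**The bias depends on coding.** A reader might infer that these patients are scored event-free and that rates are therefore biased downwards. The article states no denominator or coding, and such rules may stand in an analysis plan that is not shown. The bias is therefore conditional. The gap in the definitions is not, because both are given in full.

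**Conclusion.** The pair of definitions is wrong as written. A return of MDD after a response that stayed above 7 and lasted more than 2 months is neither relapse nor recurrence, and a duration of exactly 2 months is neither in any patient. This follows from the wording alone and rests on no assumed rate.

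The possible extent is every baseline of 16 or more. The number of patients is unknown, and a percentage from assumed HAMD-17 means and correlations would reflect those assumptions rather than this document. Understated rates or misleading prediction models follow only if the affected patients are treated as event-free.

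Nor should the point be read as covering all 14,000 patients in the same way. The naturalistic observation cohort (NOC, n=10,000) has no scheduled HAMD-17 between baseline and year 1, so its state at the end of acute treatment is not measured on schedule. The finding bears on the PMC (n=4,000).

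**What to change.** Reconcile the two definitions so that every return, by the protocol's own criterion of HAMD-17 ≥14 with DSM-5 MDD, after response or remission falls in exactly one category. One way is to analyse a combined return-of-illness event and split it by entry state (remission, or response only) and by how long that state lasted (<2 months, ≥2 months). The second split also settles the case of exactly 2 months.

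If recurrence is meant for remitters only, say so, and keep non-remitting responders out of its risk set rather than counting them as event-free.

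Apply the definitions in the PMC, where HAMD-17 is scheduled in the acute phase, and do not extend them to the NOC as if the same measurements existed there.

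The cost is endpoint wording. The PMC needs no new data. With the combined event, the reported event rate would be somewhat higher.

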#### Secondary outcomes

Hospitalization for psychiatric episodes or emotional events.Conversion to bipolar disorder: DSM-5-diagnosed manic or hypomanic episodes.High risk of suicide: score on the third item of the HAMD-17 ≥3 or answering “Yes” to item 4 or 5 of the C-SSRS.Adverse effects of drug treatment and cumulative drug exposure.Adherence to treatment, as measured with the PAQ. Not taking prescribed drugs ≥70% of the time is considered to indicate non-adherence.Changes in social functions in the acute, consolidation and maintenance phases compared with those at enrollment.Changes in cognitive function in the acute, consolidation and maintenances phase compared with those at enrollment.Changes in multi-omics, neuroimaging, electrophysiology and digital phenotype indicators.

### Data management

A multi-source central data platform will be established to accommodate the multidimensional data included in the study (Figure 3). Clinical and objective databases will be used. The clinical database contains demographic, clinical and cognitive data collected by the electronic data capture (EDC) system, while the objective database contains biospecimen, neuroimaging, EEG and digital phenotype data. The central data platform will extract multidimensional data from each data management system (e.g. neuroimaging system, EEG system and biobank). We have established standardized disease-specific cohort study dataset frames and data elements based on the Clinical Data Interchange Standards Consortium (CDISC), Standard Data Tabulation Model (SDTM) and Chinese national or industry terminology and specifications. All centers will collect data following standard operating procedures (SOP). Then, the data collected at each center will be uploaded to the local platform, transformed into a uniform format and transferred to the central data platform. Quality control will be applied at every step in this process. Each participant will be assigned a unique identification number. Other functions of the central data management platform include backup and recovery, ensuring data security and confidentiality and quality control checks on all data.

**Fig 3 Fig3:**
[figure not shown]
Data management

## Data analysis

Comprehensive data, amounting to thousands of variables across several modalities, will be collected in this project. Thus, we will be able to perform exploratory, data-driven analyses, and targeted, hypothesis-driven researches. These analyses and researches will help us investigate the trajectory of depression, identify clinical and biological subtypes of MDD, and construct prediction models of primary and secondary outcomes.

Several methods will be available to investigate changes in symptoms and facilitate an understanding of the disease trajectory, such as repeated-measures analysis of variance/mixed-effects model, time series analysis, latent variable growth curve model, multi-layer linear model and dynamic Bayesian network model. Cluster analysis, principal component analysis and other algorithms may be used to identify clinical and biological subtypes of depression.

Methods considered for the features' selection before the predictive model construction include the least absolute shrinkage and selection operator (LASSO), hierarchical LASSO and elastic net. Machine learning algorithms will then be used to build a model integrating multimodal biomarkers (multi-omics, EEG, and neuroimaging markers) and clinical features. Receiver operating characteristic (ROC) curve, cross-validity, net reclassification improvement (NRI) and integrated discrimination improvement (IDI) will be calculated to estimate and improve the performance of the model.

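### NRI and IDI are named as measures to estimate and improve the multimodal model, but both can be clearly positive when predictions are merely overconfident; added value and tuning should rest on a held-out proper score

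*Protocol article*

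**What the plan says.** The Data analysis section of the protocol article describes data "amounting to thousands of variables across several modalities" and intends to "construct prediction models of primary and secondary outcomes". Candidate methods for feature selection are the "least absolute shrinkage and selection operator (LASSO), hierarchical LASSO and elastic net". After that, "Machine learning algorithms will then be used to build a model integrating multimodal biomarkers (multi-omics, EEG, and neuroimaging markers) and clinical features".

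Four items are then listed for performance. The sentence opens with the ROC curve and cross-validation and goes on to the two reclassification measures: "net reclassification improvement (NRI) and integrated discrimination improvement (IDI) will be calculated to estimate and improve the performance of the model". The article offers its trajectory, subtype and feature-selection methods as options. These four measures are stated as a definite choice, and they are given two purposes: to measure performance and to improve it.

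The article does not say which form of NRI is meant (continuous or category), with which cut-offs, or against which reference model. Nor does it say which measure prevails if they disagree.

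**The concern.** A proper score is best, on average, when the stated risks are the true risks. NRI and IDI lack this property. Continuous NRI counts only whether a risk moved up or down, and IDI measures how far apart the mean predicted risks of events and non-events lie. A model that states the same information more boldly can therefore gain on both. The ROC curve cannot show that the risks are too extreme, because it depends on ranking alone.

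This matters for the design described. Selecting from thousands of candidate variables and then fitting machine-learning algorithms is a setting in which predictions tend to be too extreme. If NRI or IDI help to choose among models, that fault can be rewarded. If they are used to say what biomarkers add to clinical features, a positive value need not mean that anything was added.

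**Working it through.** The article gives no performance target, event rate or AUC for the models, so there is no figure to reproduce. What can be checked is the mechanism. All parameters below are assumptions.

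**Set-up.** The reference risk p is calibrated, with logit p normal about a mean μ with SD 0.8 (AUC about 0.70). Event rates are 0.12, 0.32, 0.50 and 0.68. The new model is the same predictor with its logit multiplied by k = 1.5, 2 or 3, either about μ or about 0 (risk 0.5). It holds no new information. There are 2,000,000 simulated subjects.

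**Formulas.**
- Continuous NRI = 2 × [P(up | event) − P(up | non-event)].
- IDI = discrimination slope of the new model − that of the reference, where slope = mean risk in events − mean risk in non-events.
- Brier = mean of (outcome − risk)².

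**One case by hand (event rate 0.50, k = 2).** Risks above 0.5 go up and those below go down. P(up | event) is 0.6455 and, by symmetry, P(up | non-event) is 0.3545. So NRI = 2 × (0.6455 − 0.3545) = +0.582. The reference Brier score is 0.2191; for a calibrated model the slope is 1 − 0.2191/(0.5 × 0.5) = 0.1236. The IDI of +0.072 takes the slope to about 0.196. The Brier score worsens from 0.2191 to 0.2308. The AUC stays at 0.702, since the ranking is untouched.

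**All cases.** AUC change is 0 and the Brier score worsens in every one.

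| Overconfidence | Event rate | IDI | Continuous NRI | Category NRI (cut-offs 0.5; 0.1/0.3; 0.3/0.6) |
|---|---|---|---|---|
| about the mean logit | 0.12 to 0.68 | +0.042 to +0.142 | about +0.58 | 0 to +0.29 |
| about risk 0.5 | 0.32 to 0.68 | +0.028 to +0.109 | +0.36 to +0.58 | 0 to +0.27 |
| about risk 0.5 | 0.12 | −0.010 to −0.037 | +0.02 | 0 to −0.26 |

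Stretching about the mean logit shifts the mean risk slightly unless the event rate is 0.50. With the mean risk held fixed instead, logits multiplied by 1.25 or 2, event rates of 5.5% to 68% and reference AUCs of 0.66 to 0.79, all 30 settings gave continuous NRI of +0.41 to +0.80, IDI of +0.005 to +0.094 and a worse Brier score. At a 32% event rate with AUC 0.70 and doubled logits, NRI was +0.58 and IDI +0.07, while the Brier score went from 0.193 to 0.203.

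**Noise markers, tested on independent subjects.** Three simulations:
- Unpenalised logistic models with 20 to 200 noise features, fitted on 400 to 4,000 subjects and tested on 5,000: AUC change −0.009 to −0.073, Brier worse by 0.0025 to 0.0387, continuous NRI +0.03 to +0.07, IDI −0.005 to +0.001.
- The top 30 of 1,000 noise markers, 2,800 training and 1,200 test patients: AUC change −0.02 to −0.09, mean NRI +0.014 to +0.034. With 600 events and 600 non-events, the standard error of NRI is about √(1/600 + 1/600) = 0.058, so the largest mean is 0.034/0.058 = 0.6 standard errors.
- A further check: NRI +0.000 to +0.010 with SD about 0.06, IDI slightly negative.

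**The case against.** The strongest reply has four parts.

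First, this is a condensed article. Calibration measures, the reference model and the form of NRI are commonly left to the full protocol or SAP, which are not shown. That stands: a reader might infer that the plan has no calibration assessment, but the article cannot establish this, and the absence is not part of the point. What remains is the stated use of NRI and IDI, which later calibration reporting would not by itself justify.

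Second, the ROC curve and cross-validation open the same sentence. In these simulations the AUC is flat for stretched predictions and falls for noise markers on independent data. That also stands: a careful reader of all four measures would be warned, and the false gain is confined to NRI and IDI. But the AUC cannot show that individual risks are too extreme, and no rule is given for conflicting results.

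Third, a reader might infer that both measures always reward overconfidence, or that useless markers would routinely be declared useful. The calculations do not support either. IDI can fall, category NRI can be zero or negative, and on independent data noise markers gave an IDI of about zero and an NRI that was small and often indistinguishable from zero. The large values come from stretching a correct model's logits, not from a fitted algorithm.

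Fourth, the article names no loss function or tuning criterion and states no hypothesis that biomarkers add to clinical features. It is right that tuning on NRI or IDI is a possibility left open by the word about improving the model, not a declared procedure.

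**Conclusion.** The point holds in a limited form. The article fixes NRI and IDI among the measures for estimating and improving the multimodal model. Neither is a proper score, and both can be clearly positive when predictions are only overconfident about the mean risk: continuous NRI of +0.41 to +0.80 and IDI of +0.005 to +0.094 with the mean risk held fixed, no change in AUC and a worse Brier score. These sizes rest on assumed event rates, AUCs and degrees of stretching, and on the continuous form of NRI. They show what can happen, not what PROUD's models will do. No stated figure, sample size or primary outcome is affected. This is an inexpensive improvement to a stated method, worth making before any model is built.

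**What to change.** Do not use NRI or IDI to tune the model or to judge what biomarkers add. Name a clinical-features-only reference model, and take the change in held-out log-loss or Brier score against it as the criterion, reported beside the change in AUC. If NRI and IDI are kept, label them descriptive and report them only once both models are shown to be calibrated on held-out data.

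The cost is a change of wording in the analysis plan and a little more analysis work; data collection is unaffected. The reported gain from biomarkers may turn out smaller.
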